## Abstract

**Background:**

Antimicrobial therapy with appropriate biliary drainage is considered the standard of care for acute cholangitis, but the optimal duration of antimicrobial therapy remains unknown. Seven to 10 days of antimicrobial therapy are common for the treatment of acute cholangitis, but a recent retrospective cohort study suggested a shorter duration might be effective. A shorter duration of antimicrobial therapy can be beneficial in decreasing the length of hospital stay, improving patients’ quality of life, decreasing adverse effects, and even contributing to a decrease in the occurrence of antimicrobial resistance.

**Methods/design:**

We will conduct a multi-centre, open-label, randomized, non-inferiority trial to compare short-course therapy (SCT) with conventional long-course therapy (LCT) in treating patients with acute cholangitis. SCT consists of 5-day intravenous antimicrobial therapy if the patients had clinical improvement, while at least 7 days of intravenous antibiotics will be provided to the LCT group. The primary outcome is clinical cure at 30 days after onset. Patients will be randomly assigned in an open-label fashion. A total sample size of 150 was estimated to provide a power of 80% with a one-sided α level of 2.5% and a non-inferiority margin of 10%.

**Discussion:**

This trial is expected to reveal whether SCT is non-inferior to conventional LCT or not, and may provide evidence that one can shorten the treatment duration for acute cholangitis for the benefit of patients.

**Trial registration:**

University Hospital Medical Information Network, UMIN000028382. Registered on 30 August 2017.

## Background

Acute cholangitis is a common disorder which places a substantial burden on patients and the acute care system [1–4]. Antimicrobial therapy with appropriate biliary drainage is considered the standard of care [4, 5], but the optimal duration of antimicrobial therapy remains unknown. The commonly used treatment for acute cholangitis is 7–10 days of antimicrobial therapy [5], but a recent retrospective cohort study suggested a shorter duration might be equally effective [6]. A shorter duration of antimicrobial therapy can be beneficial in decreasing the length of hospital stay, improving patients’ quality of life, decreasing the adverse effects of antibiotics such as *Clostridioides difficile* infection, and even contributing to a decrease in the occurrence of antimicrobial resistance [7–10].

In this trial, we will compare antimicrobial therapy of a shorter duration with a conventional, longer duration, to investigate whether the short-course therapy (SCT) is non-inferior to conventional long-course therapy (LCT) in terms of clinical cure and other clinically important outcomes.

## Methods/design

### Design

We will conduct a multi-centre, open-label, randomized, non-inferiority trial to compare SCT with conventional LCT in treating patients with acute cholangitis. The final trial report will follow the Consolidated Standards of Reporting Trials (CONSORT) statement and its extension to non-inferiority trials [11]. This study was registered at the University Hospital Medical Information Network under registry number UMIN000028382. The study protocol was written in accordance with the Standard Protocol Items: Recommendations for Interventional Trials (SPIRIT) guidelines (Additional file 1 shows the SPIRIT checklist). The flowchart of the study design is shown in Fig. 1.

**Fig. 1 Fig1:**
[figure not shown]
Study design. *SCT* short-course therapy, *LCT* long-course therapy, *EOT* end of treatment, *EOS* end of study

### Patients

Patients with acute cholangitis diagnosed by gastroenterologists based on findings such as fever, abdominal pain, liver function test abnormality, or imaging studies will be eligible for trial entry. If the infectious disease doctors are allowed to participate in the care of the patients, and if the treating physicians and the patients have agreed to participate in the trial, the patients are registered as potential study participants. The study participants are enrolled in this trial if they meet all of the inclusion criteria and none of the exclusion criteria.

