### Inclusion criteria

The inclusion criteria are as follows:
Patients are 20 years or older.They are diagnosed as having acute cholangitis by treating gastroenterologists.Biliary duct obstruction was removed via procedures such as endoscopic retrograde cholangiopancreatography (ERCP), or there is no evidence of biliary duct obstruction by tests such as imaging studies to begin with.

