### Exclusion criteria

The exclusion criteria are that:
The patient did not provide written informed consent.Any biliary duct obstruction was not removed.Treating physicians or the investigators judged that inclusion in the study was inappropriate.

The presence of bacteraemia is not an exclusion criterion.

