### Outcome measures

The primary outcome is clinical cure at 30 days after onset (EOS). Clinical cure is defined as disappearance of all clinical symptoms which were present upon diagnosis.

The secondary outcomes are clinical improvement after 30 days, mortality at day 30 after the diagnosis, or in-hospital mortality, occurrence of adverse effects, and recurrence or complications of acute cholangitis. Clinical improvement is defined as decrease but not disappearance of clinical symptoms which were present upon diagnosis.

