### Sample size

The primary efficacy analysis will assess the non-inferiority of the clinical cure rate of SCT compared with LCT. The margin of non-inferiority is set at 10% on the statistically acceptable tolerance and clinically acceptable margin. This margin has been used as accepted in the field of infectious diseases [12, 13]. Because non-inferiority clinical trials in infectious diseases usually cannot rely on previous placebo controlled trials to calculate and estimate inferiority margins, we decided to use the rather arbitrary number of 10% as is conventionally employed. Regarding clinical cure, we judged the margin to likely be acceptable to most patients. The non-inferiority of SCT is concluded if the upper limit of the one-sided 97.5% confidence interval (CI) for the difference in clinical response (standard SCT) is less than 10%. To achieve a power of 80% with an α level of 2.5%, assuming as stated in the previous retrospective study a clinical cure rate of 95% with standard therapy with the same cure rate in SCT [6], with a non-inferiority margin of − 10%, 75 patients are required in each group.

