### Statistical analysis

We will analyse data using both ITT and per-protocol analyses. The per-protocol analysis population will consist of all randomized patients who are not lost to follow-up and have no major protocol deviations. We will attest the non-inferiority of the primary outcome on the basis of the normal theory test for binomial proportions. We will conduct the primary analysis without adjustment of potential confounders.

Secondary outcomes will also be analysed under a non-inferiority assumption, as appropriate. Pre-defined subgroup analyses for the primary and secondary outcomes include (1) presence or absence of septic shock at diagnosis; (2) presence or absence of bacteraemia; (3) initial antibiotics covering or not covering causative organisms; (4) Gram-positive organisms causing cholangitis; and (5) quick Sequential Organ Failure Assessment (qSOFA) score.

Clinical outcomes are confirmed by the investigators either by calling the patients by telephone or seeing them at an outpatient clinic visit, or by checking the clinical chart if the patient is still hospitalized.

All *P* values are one-sided, and *P* < 0.025 is considered statistically significant. All statistical analyses will be performed using STATA version 15.0 (StataCorp, College Station, TX, USA), and R version 3.5.1 (the R Foundation for Statistical Computing, Vienna, Austria).

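### Entry requires no presenting symptom, but cure is scored only on symptoms present at diagnosis, so symptom-free patients would count as cured in both arms and pull the result towards non-inferiority

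*Protocol article*

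**What the plan says.** **Entry.** The Patients section of the Protocol article describes eligible patients as those in whom gastroenterologists diagnose acute cholangitis on "findings such as fever, abdominal pain, liver function test abnormality, or imaging studies will be eligible for trial entry". The list is illustrative and joined by "or" in its ordinary sense; no item and no combination of items is mandatory. The corresponding line under Inclusion criteria is: "They are diagnosed as having acute cholangitis by treating gastroenterologists". The other inclusion criteria concern age and the absence or removal of obstruction. Exclusion criteria covers consent, remaining obstruction and a discretionary clause: "Treating physicians or the investigators judged that inclusion in the study was inappropriate". None of these mentions symptoms.

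**Endpoint.** Outcome measures gives the primary outcome as clinical cure 30 days after onset, and then: "Clinical cure is defined as disappearance of all clinical symptoms which were present upon diagnosis". Liver tests and imaging play no part in it. Recurrence, complications and mortality are listed separately as secondary outcomes.

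**Test and size.** Under Sample size: "The margin of non-inferiority is set at 10% on the statistically acceptable tolerance and clinically acceptable margin". The calculation assumes "a clinical cure rate of 95% with standard therapy with the same cure rate in SCT", with one-sided alpha 2.5% and power 80%, and arrives at 75 patients per arm.

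**Analysis sets.** Statistical analysis plans both ITT and per-protocol analyses. The per-protocol set drops only patients lost to follow-up or with major deviations.

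**The concern.** Entry rule and endpoint do not fit together. Two of the four findings named for diagnosis, liver tests and imaging, do not enter the outcome. A patient diagnosed on those two, without fever or pain, meets every listed criterion, yet has nothing that needs to disappear. Under the definition as written that patient is a cure on day 30 in either arm, even after a relapse with new symptoms.

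Patients whose outcome is fixed in advance add identical results to both arms and carry no information about treatment duration. In a superiority trial this would work against the sponsor's hypothesis. In a non-inferiority trial it works in favour of it. Running both ITT and per-protocol analyses does not protect against it, because a symptom-free patient who completes follow-up without a major deviation is in both sets.

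This is more than detail that an article leaves to a fuller document. Eligibility and the primary endpoint are both stated, and the problem comes from what the two stated rules produce together.

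**Working it through.** **Inputs from the Protocol article:** cure 95% in both arms, margin 10 percentage points, one-sided alpha 2.5%, power 80%, 1:1 allocation, 75 per arm.

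**Assumed inputs:** the share a of patients with no symptom at diagnosis, equal in both arms (2% to 30%), and a true cure rate among symptomatic patients of 95% (LCT) v 85% (SCT), a deficit exactly equal to the margin.

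**Step 1: the plan's own figure.** n per arm = 2 × 0.95 × 0.05 × (1.960 + 0.842)² / 0.10² = 74.56, rounded up to 75. Power at 75 per arm is 80.2%. The sample size reproduces and is not in question.

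**Step 2: dilution.** With symptom-free patients scored as cured:

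- LCT cure overall = a + (1 - a) × 0.95
- SCT cure overall = a + (1 - a) × 0.85
- difference overall = (1 - a) × 0.10

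**Step 3: chance of declaring non-inferiority.** P = Φ[(0.10 - difference)/SE - 1.96], where SE = √{[p_L(1 - p_L) + p_S(1 - p_S)]/75}.

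Worked for a = 10%: p_L = 0.955, p_S = 0.865, difference = 0.090. SE = √{[0.955 × 0.045 + 0.865 × 0.135]/75} = 0.0462. P = Φ(0.010/0.0462 - 1.96) = Φ(-1.743) = 4.1%.

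| Assumed share a | Overall difference (points) | P, normal approximation | P, exact enumeration of the Wald rule | Deficit in symptomatic patients that shows as 10 points overall |
|---|---|---|---|---|
| 0 | 10.0 | 2.5% | 3.7% | 10.0 |
| 2% | 9.8 | 2.75% | 4.1% | 10.2 |
| 5% | 9.5 | 3.2% | 4.7% | 10.5 |
| 10% | 9.0 | 4.1% | 6.0% | 11.1 |
| 20% | 8.0 | 6.6% | 9.7% | 12.5 |
| 30% | 7.0 | 10.9% | 15.5% | 14.3 |

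The exact column already starts at 3.7% with a = 0. That excess belongs to the Wald test at this sample size and not to eligibility, so only the movement down each column is relevant here.

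**Step 4: sensitivity to the base rate.** If 95% is taken as the LCT cure rate of the whole enrolled population, symptomatic LCT cure is 1 - 0.05/(1 - a). With the same 10-point deficit among symptomatic patients, the normal-approximation values become 2.75%, 3.2%, 4.0%, 6.3% and 9.75% at a = 2%, 5%, 10%, 20% and 30%. The picture does not change.

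**The case against.** **Enrolment on tests alone.** A reader might infer that the protocol provides for enrolment on liver tests or imaging alone. It does not say so. The entry condition is a specialist's diagnosis of an acute infection, the list only gives examples of evidence, and the endpoint wording presupposes that symptoms exist. Investigators may also exclude anyone they judge unsuitable. What stands is that no stated rule requires a symptom, and the discretionary clause is not tied to symptoms.

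**Cannot fail.** This is the literal result of the definition, but the article does not spell out how a patient without presenting symptoms is scored. Such a patient might be called unassessable, and the unseen full protocol might say so. Trial oversight also lists an Event Adjudication Committee, with no remit described. These points soften the claim. They do not remove it, because the definition as printed yields cure, and the Discussion says that investigators who know the allocation will judge outcomes.

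**Inflated type I error.** A reader might take the 4.1% to 10.9% as type I error above 2.5%. The documents do not support that. The margin is stated for the enrolled population, and overall deficits of 9, 8 and 7 points lie inside it. The figures describe a weakened ability to detect a 10-point deficit among symptomatic patients.

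**Size.** The shares are assumed. At 2% the effect is negligible. This objection stands in full.

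**Changing the primary population.** One might want to make symptomatic patients the primary set. The trial is open-label and already recruiting, and that would replace the stated ITT analysis. It would also cost power: with 67.5, 60 and 52.5 symptomatic patients per arm (75 × 0.9, 0.8, 0.7), power at 95% v 95% falls from 80% to about 76%, 71% and 65%. This objection also stands, and the fix below respects it.

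**Conclusion.** The point holds as a mismatch between two stated core rules. Patients without a presenting symptom may be enrolled, and under the printed definition they count as cured in either arm. The bias can go only one way, towards non-inferiority, and neither planned analysis set filters it out.

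Its size is unknown because the article gives no share of such patients. Over assumed shares of 2% to 30%, the chance of accepting a regimen 10 points worse in symptomatic patients goes from 2.5% to between 2.75% and 10.9%. This rests on equal shares in both arms, literal scoring as cured, 75 per arm and the normal approximation. It also counts fever as a presenting symptom; if fever were treated as a sign only and left out of the cure definition, more patients would be affected.

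It is a loss of assay sensitivity, possibly a small one. It does not show that the sample size is wrong or that the stated test exceeds its nominal level. A cheap correction is worthwhile; a change of primary analysis is not warranted.

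**What to change.** 1. **Inclusion criteria, for further enrolment:** add that at least one clinical symptom or sign used in the cure definition is documented at diagnosis, and name the symptoms and signs that count.
2. **Primary analysis:** leave the ITT population as it is.
3. **Sensitivity analysis:** pre-specify the primary outcome restricted to randomised patients with at least one such symptom recorded at diagnosis. Because diagnosis precedes allocation, the restriction uses a baseline characteristic and the comparison remains randomised. Report the number without any symptom in each arm, so that the share a is known.

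**Cost.** One eligibility line and one analysis line. No new data item should be needed, since presenting symptoms must already be recorded to score cure. Symptom-free patients, probably a small share, would no longer be eligible. The restricted analysis loses some power, about 76% against 80% if 10% of patients have no symptom, so it should be read alongside the ITT result and not as a second confirmatory test.

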### Inclusion criteria

The inclusion criteria are as follows:
Patients are 20 years or older.They are diagnosed as having acute cholangitis by treating gastroenterologists.Biliary duct obstruction was removed via procedures such as endoscopic retrograde cholangiopancreatography (ERCP), or there is no evidence of biliary duct obstruction by tests such as imaging studies to begin with.

### Exclusion criteria

The exclusion criteria are that:
The patient did not provide written informed consent.Any biliary duct obstruction was not removed.Treating physicians or the investigators judged that inclusion in the study was inappropriate.

The presence of bacteraemia is not an exclusion criterion.

### Ethics and informed consent

The clinical trial will be carried out according to the principles of the Declaration of Helsinki and Ethical Guidelines for Medical and Health Involving Human Subjects published by the Ministry of Health, Labour and Welfare of Japan and the Japanese Ministry of Education, Culture, Sports, Science and Technology. The study protocol was approved by the ethics committees of the participating hospitals. Written informed consent will be obtained from all patients or their representatives.

### Randomization and allocation concealment

Patients are randomly allocated to each treatment arm at a 1:1 ratio before or within 24 h after initiating antimicrobial therapy. Randomization will be performed using a stochastic minimization procedure centrally at the study centre (Division of Infectious Diseases Therapeutics, Kobe University Graduate School of Medicine). We will use an electronic data capture system to conduct randomization and data collection.

### Trial interventions

The antibiotics given to the study participants should be commercially available and approved for use in Japan. They will be used at the marketed accepted dosage as indicated in each package insert. The initial antibiotics will be selected at the discretion of either the treating physician or the consultant infectious disease doctor. Selected antibiotics can be changed to other antibiotics during the treatment based on culture/susceptibility tests results or potential adverse reactions that are suspected or occurred in the patient. Dose adjustments based on patients’ renal function or other criteria are performed as judged appropriate and necessary by the consultant infectious disease doctors.

In the SCT group, intravenous antibiotics will be continued at least for 5 days, and can be discontinued if all of the following criteria are fulfilled: (1) maintenance of body temperature under 37.8 °C for more than 48 h, (2) systolic blood pressure above 90 mmHg, (3) heart rate below 100 beats/min, (4) respiratory rate below 24 breaths/min, and oxygen saturation at room air above 90%. In the LCT group, intravenous antibiotics will be given for the duration of usual care, at least for 7 days, at the discretion of both the treating gastroenterologists and the consultant infectious disease doctors, provided that there are no biliary duct obstructions remaining, as stated in the inclusion/exclusion criteria. In the SCT group, positive blood culture results will not alter the duration of the treatment unless other complications which necessitate prolongation of the treatment, such as abscess or infective endocarditis, occur and either the treating physicians or the consultant infectious disease doctors remove the patient from the intervention. These patients will still be included in the analysis on an intention-to-treat (ITT) basis but will be excluded from the per-protocol analysis. The schedule of assessments is shown in Fig. 2.

**Fig. 2 Fig2:**
[figure not shown]
Schedule of assessments. *EOT* end of treatment, *EOS* end of study, *qSOFA* quick Sequential Organ Failure Assessment

### Assessment and follow-up

Clinical assessment is performed at baseline and daily throughout the study treatment, at the end of therapy (EOT), and at discharge from the hospital or 30 days after onset (end of study, EOS).

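### Daily assessment stops with study treatment, so mild adverse effects may be ascertained unequally between SCT and LCT

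*Protocol article*

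**What the plan says.** The protocol article, Assessment and follow-up, gives one schedule for both arms: "Clinical assessment is performed at baseline and daily throughout the study treatment, at the end of therapy (EOT" and finally "at discharge from the hospital or 30 days after onset (end of study, EOS". No assessment is named between the end of therapy and that last one.

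Trial interventions sets the length of treatment by arm. For short-course therapy (SCT), "In the SCT group, intravenous antibiotics will be continued at least for 5 days, and can be discontinued if all of the following criteria are" met. For long-course therapy (LCT), "intravenous antibiotics will be given for the duration of usual care, at least for 7 days". Neither arm has a stated maximum. A positive blood culture does not lengthen SCT "unless other complications which necessitate prolongation of the treatment, such as abscess or infective endocarditis, occur".

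Among the secondary outcomes listed under Outcome measures are "occurrence of adverse effects, and recurrence or complications of acute cholangitis". Statistical analysis says that secondary outcomes are also examined for non-inferiority where appropriate. It adds that clinical outcomes are confirmed by telephone, at an outpatient visit, or from the chart for patients still in hospital.

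**The concern.** Treatment length is the randomised difference, and daily assessment lasts as long as treatment. How closely a patient is watched is therefore partly a consequence of allocation, and it differs on the very days when the arms differ. An SCT patient who stops on day 5 has no further scheduled assessment until discharge or day 30. An LCT patient is still seen daily on days 6 and 7, and possibly longer. A short episode of diarrhoea or a rash on those days would be seen in LCT. In SCT it might have to be remembered weeks later.

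Three features make this matter. First, the Background and the Discussion both name fewer adverse effects as a benefit of SCT, and under-recording in SCT pushes towards that conclusion. Second, in a non-inferiority reading of a secondary outcome, events missed in the experimental arm favour non-inferiority. Third, the trial is open-label and its investigators judge the outcomes, so blinding does not offset unequal observation.

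A higher count in LCT could also be a true effect of longer antibiotic exposure. Under this schedule the exposure effect and the detection effect cannot be told apart.

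**Working it through.** **Inputs from the protocol article.** Minimum treatment is 5 days in SCT and 7 in LCT (Trial interventions). On usual practice, "The commonly used treatment for acute cholangitis is 7–10 days of antimicrobial therapy" (Background). Both arms are read at day 30 (Outcome measures). Cure rate 95% in both arms, margin 10 points, one-sided 2.5%, power 80%, 75 per group (Sample size).

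**Assumptions not in the documents.** A true daily risk *h* of a mild event, equal in both arms, and a share *r* of events after treatment that is recovered at the final contact. Events during treatment are taken as always detected. For simplicity, day 30 is counted from the start of treatment.

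**Step 1: the plan's own figure.** n = (1.960 + 0.842)² × 2 × 0.95 × 0.05 / 0.10² = 7.85 × 0.095 / 0.01 = 74.6, so 75 per group. Power at 75 is 80.2%. The stated size reproduces, and nothing about the assessment schedule enters it. The article gives no figure for detection of adverse effects.

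**Step 2: difference in days of daily assessment (LCT minus SCT).**

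| SCT days | LCT days | Difference |
|---|---|---|
| 5 | 7 | 2 |
| 5 | 10 | 5 |
| 7 | 7 | 0 |
| 8 | 7 | −1 |

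**Step 3: apparent event rate with T treatment days.** P(T) = 1 − (1 − h)^T × (1 − h·r)^(30 − T). With h = 2%, for 5 versus 7 days:

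- r = 0: 1 − 0.98^5 = 9.6% against 1 − 0.98^7 = 13.2%; gap 3.6 points.
- r = 0.5: 1 − 0.98^5 × 0.99^25 = 29.7% against 1 − 0.98^7 × 0.99^23 = 31.1%; gap 1.4 points.
- r = 0.9: 42.6% against 42.8%; gap 0.2 points.
- r = 1: 45.5% in both; gap 0.

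Gaps in percentage points for other assumed risks, 5 versus 7 days:

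| Share recovered r | h = 0.5% | h = 1% | h = 2% |
|---|---|---|---|
| 0 | 1.0 | 1.9 | 3.6 |
| 0.5 | 0.5 | 0.8 | 1.4 |
| 0.9 | 0.1 | 0.2 | 0.2 |
| 1 | 0 | 0 | 0 |

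**Step 4: other durations, h = 2%.**

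- 5 versus 10 days, r = 0: 9.6% against 18.3%; gap 8.7 points.
- 5 versus 10 days, r = 0.5: 29.7% against 1 − 0.98^10 × 0.99^20 = 33.2%; gap 3.5 points.
- 7 versus 7 days: gap 0.
- 8 versus 7 days, r = 0: 14.9% against 13.2%; the gap reverses to −1.7 points.

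**Step 5: in patients.** With 75 per arm and h = 2%, the 5-versus-7-day gaps are 75 × 0.0358 = 2.7 patients (r = 0), 75 × 0.0141 = 1.1 (r = 0.5) and 75 × 0.0023 = 0.2 (r = 0.9).

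**The case against.** A reader might infer that every LCT patient is examined on two or more extra days, and that adverse effects and complications are bound to be found more often in LCT. The documents do not support that, for these reasons.

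- Five days is a floor for SCT. Stopping requires all the stability criteria, and a complication may lengthen treatment. The two-day difference holds only for an SCT patient who stops on day 5.
- Both arms share the final assessment, and the means of confirming outcomes does not differ by arm. If that contact recovers everything, no gap remains.
- Trial oversight provides for immediate reporting of deaths and serious adverse events, which is not tied to assessment days. The concern is therefore about mild or transient events.
- For recurrence and complications the direction is open. Late events fall after the end of therapy in both arms, and a complication that prolongs SCT also prolongs its daily assessment.

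All of this stands, and it limits the point. It does not remove it. The confirmation rule under Statistical analysis speaks of clinical outcomes and does not mention adverse effects. Assessment and follow-up lets the last assessment fall at discharge, whereas Outcome measures fixes it at day 30. If SCT shortens the stay, as the authors expect, the last assessment could on that reading come earlier in SCT.

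It can also be said that Fig. 2 or the full protocol may list further contacts. Fig. 2 could not be read here, so this is possible. The text nevertheless states a schedule, and an analysis plan cannot recover events that were never collected.

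**Conclusion.** The point holds for the ascertainment of mild or transient adverse effects. The window of close observation depends on treatment length, and recording may be unequal, probably lower in SCT after treatment stops. For recurrence and complications inequality is possible but its direction is not established. The primary outcome is read at day 30 in both arms, so it and the sample size are unaffected.

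The size is not fixed by the design. At an assumed 2% per day and 5 versus 7 days, it runs from 3.6 points with no later recovery to 0 with full recovery. The 3.6-point figure, and the 8.7 points for 5 versus 10 days, are upper bounds at that risk for those durations. These figures rest on an equal true daily risk and complete detection during treatment, neither of which the documents give. The issue is confined to secondary outcomes, but one of them carries a main claimed benefit of SCT.

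**What to change.** State in the protocol that adverse effects, recurrence and complications are compared between arms over one window, from randomisation to day 30 after onset. Put the same fixed list of questions to every patient in both arms at the day-30 contact already planned under Statistical analysis. Hold that contact at day 30 for everyone, not at discharge when discharge is earlier, and reword Assessment and follow-up to agree with Outcome measures.

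Keep every recorded event in the report. Note for each event when and how it was found, and add a sensitivity comparison that excludes, in both arms, events found only by daily checks after day 5. That comparison also removes some genuine effects of longer exposure, so it should stand beside the main count and not replace it.

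The cost is slightly more data collection at an existing contact and some reliance on recall. Matching daily assessments in both arms would rely less on recall, but it would need extra contacts with SCT patients who may already have gone home, so it is not needed as the first choice.

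### The end-of-study assessment can be read as discharge or day 30, which conflicts with a primary outcome fixed at day 30 after onset

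*Protocol article*

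**What the plan says.** Four places in the Protocol article bear on when the primary outcome is assessed.

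- **Assessment and follow-up** lists assessments at baseline, daily on treatment, at end of therapy, and finally "at discharge from the hospital or 30 days after onset (end of study, EOS"). It does not say which alternative applies to whom, or whether the EOS label covers both.
- **Outcome measures** states: "The primary outcome is clinical cure at 30 days after onset (EOS"). Cure is a symptom state: "Clinical cure is defined as disappearance of all clinical symptoms which were present upon diagnosis". Mortality, a secondary outcome, is given as "mortality at day 30 after the diagnosis, or in-hospital mortality".
- **Statistical analysis** says that investigators confirm outcomes "either by calling the patients by telephone or seeing them at an outpatient clinic visit", or from the chart for patients still in hospital. It gives no day or window.
- **Trial interventions** sets the minimum intravenous course. For SCT: "In the SCT group, intravenous antibiotics will be continued at least for 5 days". For LCT: "intravenous antibiotics will be given for the duration of usual care, at least for 7 days". Background and Discussion both expect a shorter hospital stay with a shorter course.

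**The concern.** One label, EOS, is attached to day 30 in one section and, on one reading, to discharge or day 30 in another. The two alternatives are joined by "or". Even if the label belongs only to day 30, the sentence still lets a discharge assessment stand in place of the day-30 one.

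This matters because discharge happens after randomization and is probably affected by arm. If discharge served as the endpoint time, SCT patients would tend to be assessed earlier than LCT patients, in an open-label trial whose endpoint is a symptom state judged by investigators. A patient who is symptom-free at discharge and relapses later would count as cured. Recurrence is collected, but only as a secondary outcome. The comparison would then no longer be the day-30 difference to which the 95% cure assumption and the 10% margin are applied in Sample size.

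**Working it through.** **1. The passages side by side**

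| Section | Time given | Label |
|---|---|---|
| Assessment and follow-up | discharge, or 30 days after onset | EOS (scope unclear) |
| Outcome measures, cure | 30 days after onset | EOS |
| Outcome measures, mortality | day 30 after diagnosis, or in hospital | none |
| Statistical analysis, confirmation | no day given | none |

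The conflict lies between the first two rows. The fourth row points to contact after discharge but does not date it.

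**2. The plan's own sample size**

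Inputs from Sample size: cure 95% in both arms, margin 10 points, one-sided α 2.5%, power 80%.

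n per arm = (1.960 + 0.842)² × (0.95×0.05 + 0.95×0.05) / 0.10² = 74.6, rounded up to 75.

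The stated 75 per group is reproduced (power at 75: 80.2% by the normal approximation). The timing question does not alter it.

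**3. What missed failures would do (illustration)**

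Assumptions that are not in the documents:

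- True day-30 cure is 95% in LCT and 85% in SCT. The difference equals the margin, so any non-inferiority claim is false.
- A share f of day-30 failures has not yet occurred at discharge and is recorded as cure, with the same f in both arms.
- Every patient is assessed at discharge.

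Recorded cure: LCT = 1 − 0.05(1 − f); SCT = 1 − 0.15(1 − f).

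Normal approximation: P(claim) = Φ((0.10 − d)/SE − 1.96), where d is the recorded LCT − SCT difference and SE = √[(p_L(1 − p_L) + p_S(1 − p_S))/75]. For f = 0.2: d = 0.08 and SE = √[(0.96×0.04 + 0.88×0.12)/75] = 0.0438, so Φ(0.456 − 1.96) = 6.6%.

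The exact column sums the binomial probabilities of all outcome pairs for which the upper Wald 97.5% limit of the difference lies below 10%.

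| Missed share f | Recorded LCT v SCT | d | Normal approximation | Exact Wald |
|---|---|---|---|---|
| 0 | 95.0% v 85.0% | 10 points | 2.5% | 3.7% |
| 10% | 95.5% v 86.5% | 9 points | 4.1% | 6.0% |
| 20% | 96.0% v 88.0% | 8 points | 6.6% | 9.7% |
| 30% | 96.5% v 89.5% | 7 points | 10.9% | 15.5% |
| 50% | 97.5% v 92.5% | 5 points | 29.3% | 36.4% |

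This table shows equal under-ascertainment in both arms. An extreme version of differential timing, with failures missed in SCT only, gives exact Wald values of 12.9%, 22.0% and 52.0% for f = 20%, 30% and 50%.

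**4. The opposite direction**

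Take f = 50% in both arms and suppose that, in addition, 5 points of SCT patients still have symptoms at the earlier assessment. Recorded cure is then 97.5% v 87.5%, d is back to 10 points, and the exact Wald probability falls from 36.4% to 4.8%. The sign and size of any bias therefore depend on quantities that the documents do not give.

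**The case against.** The strongest reply is that the primary outcome is not in doubt. In Assessment and follow-up the parenthesis directly follows the words for day 30 and can attach to that alone, leaving discharge as a separate assessment. Outcome measures, which governs the endpoint, says day 30. Statistical analysis plans telephone or clinic contact, which would not be needed if follow-up ended at discharge. The schedule of assessments (Fig. 2) and the full protocol are not available here, and either may settle the matter.

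Most of this stands, and it makes a day-30 assessment in both arms the likelier intent. It does not remove the conflict: the sentence in Assessment and follow-up still offers discharge as an alternative, and the contact sentence has no date with which to overrule it.

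A reader might infer that the plan prescribes assessment at different times in the two arms, or that it carries a 36% risk of a false claim. The documents support neither inference. Differential timing follows from only one reading of one sentence. The 36% figure rests on an unsourced 50% missed share, applied equally to both arms, with every patient assessed at discharge; it does not measure arm-dependent timing. Nor can discharge be equated with the last day of intravenous therapy, since the stated durations are minima.

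A reader might also see bias in the different time origins, onset for cure and diagnosis for mortality. Treatment cannot shift either origin, so this is a matter of clarity.

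**Conclusion.** The point holds as an unreconciled statement of the primary endpoint's timing, and it should be fixed. It is not an established bias. If discharge were used, assessment time would probably depend on arm and later relapse would be missed, but symptoms still unresolved at an early assessment could push the result against SCT. Under the stated assumptions, and relative to 3.7% with full ascertainment, false non-inferiority would range from 6.0% to 36% for equal missed shares of 10% to 50%. Those shares are illustrative. No figure in the plan is wrong, and 75 per group stands. The alternative wording for mortality is a minor, secondary matter.

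**What to change.** - In Assessment and follow-up, define EOS as day 30 after onset, with a short stated window, for every patient in both arms whatever the discharge date. List discharge as a separate assessment that does not carry the EOS label.
- In Statistical analysis, tie the telephone, clinic or chart confirmation to that day and window, identically in both arms. Check that Fig. 2 agrees.
- Minor: report day-30 all-cause mortality and in-hospital mortality as two separate outcomes, not as alternatives.

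The cost is wording and an assessment-date field in the data capture system. Contact after discharge is already provided for, and the sample size does not change.
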